### ***Serious Adverse Event***

A serious adverse event (SAE) is any untoward medical occurrence that at any dose:

- Results in death.
- Is life-threatening.

NOTE: The term “life-threatening” in this definition refers to an event in which the subject is at risk of death at the time of the event; it does not refer to an event that hypothetically might cause death if it were more severe.

- Requires inpatient hospitalization or prolongation of existing hospitalization.
- Results in persistent or significant disability/incapacity.
- Is a congenital anomaly/birth defect.
- Is otherwise considered as medically important.

Important medical events that may not result in death, be life-threatening, or require hospitalization may be considered as SAEs when, based upon appropriate medical judgment, they may jeopardize the subject or may require medical or surgical intervention to prevent one of the outcomes listed in this definition. Examples of such events include allergic bronchospasm requiring intensive treatment in an emergency room or at home, blood dyscrasias or convulsions that do not result in inpatient hospitalization.

Relevant serious adverse events that need to be intensively monitored in this trial:

1. III Degree atrioventricular block;

2. Severe asthma attack;
3. Cardiac arrest
4. Acute pulmonary edema;
5. Worsening heart failure;
6. Shock.

### **Events that Do Not Meet the Definition of an SAE**

Elective hospitalizations to simplify study treatment or study procedures are not considered an SAE. However, all events leading to unplanned hospitalizations or unplanned prolongation of an elective hospitalization must be documented and reported as SAEs.

#### **7.4.1.2 Recording Adverse Events**

All adverse events occurring during the study, whether serious or not, must be recorded in the Case Report Form (CRF), including its description, severity, duration (onset and resolution dates), causal relationship (i.e., whether the adverse event is related to the study treatment), any other potential causal factors, actions taken with the study drug (dose reduction, withdrawal...), required treatment, and outcome. In addition, for all serious adverse events, seriousness criteria must be documented and a specific safety report form must be completed.

#### **7.4.1.3 Expedited Reporting of Serious Adverse Events**

As soon as the Investigator detects a serious adverse event, as defined above, associated with the study medication, he/she will report it within 24 hours (by e-mail, phone, or fax) to principal investigator [name].

The Investigator must promptly respond to any request for follow-up information or questions from the Sponsor. Serious adverse events occurring during the study must be monitored and followed up by the Investigator until stabilization or until the outcome is known, unless the subject is lost to follow-up. The Investigator will ensure any necessary additional therapeutic measures and follow-up procedures.

Reporting procedures and timelines for any new information on a previously reported serious adverse event (follow-up) are the same as for the original report.

Further to reporting serious adverse events to the Sponsor, the Investigator will comply with any applicable local pharmacovigilance requirements to report adverse reactions/events to national pharmacovigilance systems.

#### **7.4.3 Other laboratory tests**

During the study period, laboratory tests other than these specified in the protocol will be

decided based on the needs of clinical conditions.

## **8 Statistics**

### **8.1 Sample Size**

This study will recruit 110 patients with  $RHR \geq 70$  bpm and mild or moderate blood pressure.

### **8.2 Randomization**

Patient will be randomized in a 1:1 ratio.

### **8.2 Randomization**

All subjects will be treated according to the dose approved for their condition, and the subsequent treatment will be carried out according to the standard care and medical practice of the study site. Therefore, no randomization is required for this study.

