| Study objectives             | 
Primary objective
 
To compare the efficacy in SNS activity and central blood pressure(CAP) of bisoprolol and atenolol in essential hypertensive patients with RHR>70bpm
 
Secondary objective
 
 
1. To compare the effect in other SNS indication of bisoprolol and atenolol in EH patients with RHR>70bpm
 
2. To compare the efficiency of bisoprolol and atenolol to attaining RHR<65bpm]
 
3. To compare the efficiency of bisoprolol and atenolol on peripheral blood pressure
 
4. To compare the safety and compliance of bisoprolol and atenolol treatment after RHR<65bpm
 
 |
| Study design and plan        | 
A phase IV single-centre randomize controlled study. The patient will receive bisoprolol 5mg Qd.(or atenolol 25mg Bid) for 2 weeks. If his/her heart rate<65bpm, this initial dose will be prolonged for another 2 weeks before the observation is over.
 
If the heart rate>65bpm, the patient will receive bisoprolol 7.5mg Qd.( or atenolol 37.5mg Bid) for 2 weeks. Then if his/her heart rate<65bpm, this
                                                                                                                                                                                                                                                  |

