## **4. Study Objectives**

### **Primary objective**

To compare the efficacy in SNS activity and central blood pressure(CAP) of bisoprolol and atenolol in essential hypertensive patients with RHR>70bpm

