## 5. Study Design

### 5.1 Study Design

It is a single-centers, randomized study in China, and planned to enroll 110 essential hypertension patients from 1 sites, who will be assigned to two groups randomly. All the inclusive patients will be consistent with the diagnosis of essential hypertension, and have a resting heart rate(RHR)  $\geq 70$  beats per minutes(bpm).

The inclusive patients will be assigned to two groups as follow (ratio 1:1)

Arm A: bisoprolol, 5-10mg/day for a targeting heart rate of less than 65 bpm(96)

Arm B: atenolol, 50-100mg/day for a targeting heart rate of less than 65 bpm (96)

The patient will receive bisoprolol 5mg Qd.(or atenolol 25mg Bid) for 2 weeks. If his/her heart rate<65bpm, this initial dose will be prolonged for another 2 weeks before the observation is over.

If the heart rate>65bpm, the patient will receive bisoprolol 7.5mg Qd.( or atenolol 37.5mg Bid) for 2 weeks. Then if his/her heart rate<65bpm, this increased dose will be prolonged for another 2 weeks before the observation is over.

If the heart rate>65bpm, the patient will receive bisoprolol 10mg Qd.( or atenolol 50mg Bid) for 2 weeks. Then if his/her heart rate<65bpm, this increased dose will be prolonged for another 2 weeks before the observation is over. If the heart rate>65bpm, the observation is over directly.

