### **5.3.4 Randomization:**

This study is a parallel, randomized, controlled study, Patient will be randomized by the predesigned randomization schedule using randomization envelope.

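### Two sections numbered 8.2 contradict each other on whether patients are randomised; the second should be deleted

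*Protocol*

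**What the plan says.** The protocol addresses allocation in five places.

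- **Synopsis, study design and plan:** "A phase IV single-centre randomize controlled study".
- **Section 5.1, Study Design:** 110 patients are planned, "who will be assigned to two groups randomly", in a 1:1 ratio.
- **Section 5.3.4, Randomization:** "Patient will be randomized by the predesigned randomization schedule using randomization envelope".
- **Section 8.2, first entry:** "Patient will be randomized in a 1:1 ratio".
- **Section 8.2, second entry, directly after the first and with the same number and title:** subjects receive the approved dose for their condition, and "the subsequent treatment will be carried out according to the standard care and medical practice of the study site". The section then draws its conclusion: "Therefore, no randomization is required for this study".

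The primary objective is comparative: "To compare the efficacy in SNS activity and central blood pressure(CAP) of bisoprolol and atenolol in essential hypertensive patients with RHR>70bpm". Section 8.3.1 makes BRS and central blood pressure, both measured at the last visit, the primary endpoint.

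**The concern.** One chapter states two rules for how patients come to be on one drug or the other, and the rules exclude each other. The second is more than a stray heading. It gives a reason, draws a conclusion with a connecting word, and sits in the chapter that governs the analysis. A site, an ethics committee, an auditor or a journal could read it as deliberate.

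The trial's main question is a between-drug comparison, and random allocation is what protects it from confounding. If the second 8.2 were applied, that protection would be gone, and the protocol describes nothing in its place. If it were ignored in practice, the approved document would still say that randomisation was not needed, and the claim to be a randomised trial could be disputed on the protocol's own words.

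The same paragraph also describes treatment as usual site practice, whereas sections 5.1 and 6.2 prescribe it.

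**Working it through.** No formula applies. The check is a comparison of texts.

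**Step 1. Can both 8.2 entries hold?** The first requires randomisation at 1:1. The second says none is required. The paragraph says nothing to confine itself to one group, period or subset of patients, so no reading satisfies both.

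**Step 2. Is the second entry superseded?** The protocol text has no amendment log or later passage that withdraws it. Both entries are current text.

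**Step 3. Which entry agrees with the rest?**

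| Place | Allocation |
|---|---|
| Synopsis | Randomised, controlled |
| 5.1 | Random, two groups, 1:1 |
| 5.3.4 | Schedule prepared in advance, envelopes |
| 8.2, first entry | Randomised, 1:1 |
| 8.2, second entry | None required |

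Four places describe random allocation and one denies it. The ratio comes from 5.1 and the first 8.2; the mechanism comes from 5.3.4. Together they give a complete rule without the second 8.2, so no new design decision is needed.

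**Step 4. Does the treatment wording agree?** Section 5.1 sets two-week steps, with the move to the next step decided by whether heart rate is below 65 bpm. Section 6.2 also sets fixed treatment periods. The second 8.2 instead refers treatment to the site's own practice. These passages must be reconciled. Sections 5.1 and 6.2 also differ from each other (for example, atenolol is twice daily in 5.1 and once daily in 6.2). That is a separate matter, but it bears on what the corrected text can point to.

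**Step 5. Where might the paragraph have come from?** It reads like text carried over from a non-randomised study of one drug. That is an inference, but other parts of the protocol fit it:

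- Withdrawal for intolerance (5.3.5) names Concor only.
- Adverse-event causality (7.4.1.1) is assessed against Concor only.
- The section on non-permitted medicines excludes beta-blockers other than Concor, which read literally would cover atenolol.

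The contradiction stands with or without this explanation.

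**Step 6. Does the protocol offer a fallback?** Section 8.5.1 gives a significance level, confidence intervals and a rule for missing data. The protocol describes no adjustment for confounders or other method for a non-randomised comparison. A statistical analysis plan might add one, but it could not settle whether patients are randomised; that is for the protocol.

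**The case against.** The strongest reply is that the harmful reading is unlikely. Four places specify randomisation, and a site working from 5.3.4 would use the envelopes. The protocol shows similar editing residue elsewhere: two sections numbered 6.3, 7.1 used twice, and the objectives repeated. On this view the paragraph is leftover text and the problem is one of documentation.

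Much of this stands. The weight of the text shows that randomisation is intended, and the point rests on the contradiction itself, not on a forecast that the envelopes will be ignored. But the paragraph remains current and contradicts the feature on which the primary comparison depends, so it is more than clerical.

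A reader might also infer more than the protocol supports:

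- **That physicians choose between the two drugs.** The second 8.2 speaks of dose and subsequent care. It does not say who would choose between bisoprolol and atenolol.
- **That no causal comparison would remain.** A non-randomised comparison can be made with adjustment and an assumption of no unmeasured confounding. What would be lost is the randomised basis.
- **That the damage can be stated as a false-positive rate.** Any such figure needs an assumed prognostic imbalance between the arms, and the protocol gives no source for one. It would also apply only under the unlikely reading. A figure of this kind would be purely hypothetical, so none is given here.
- **That the timing of envelope opening is at fault.** Section 5.3.4 is silent on timing, and nothing in this contradiction shows a defect there.

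**Conclusion.** The contradiction is real and must be corrected. The second 8.2 is wrong as written: it conflicts with the first 8.2, the synopsis and sections 5.1 and 5.3.4 on allocation, and with 5.1 and 6.2 on treatment.

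Its size is qualitative. If the paragraph were applied, the entire primary comparison, planned on 110 patients, would lose its randomised basis and be open to confounding. If it is not applied, the harm is to the credibility of the trial's status as randomised. It would go too far to conclude that the trial is not randomised; the document as a whole points the other way.

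The conclusion assumes only that the text at hand is current. That randomisation is intended is inferred from the four agreeing places. Whether any patient was allocated without randomisation cannot be told from the protocol.

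**What to change.** By amendment:

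1. Delete the whole second section 8.2.
2. Keep a single section 8.2 consistent with 5.1 and 5.3.4: 1:1 allocation from the schedule prepared in advance, using envelopes.
3. Reconcile the description of treatment with sections 5.1 and 6.2, so that the Statistics chapter no longer describes a different treatment regime.
4. If any patient was allocated without randomisation, document it.

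The cost is the removal of one paragraph. Design, sample size and procedures stay as they are, provided that no patient was allocated under the deleted text. If any was, the documentation in step 4 is added work.

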### **8.3 Endpoints**

#### **8.3.1 Primary Endpoint(s)**

The primary endpoint is BRS and central blood pressure at Last visit.

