### 3. Background

The sympathetic nervous system (SNS) plays a role in the pathophysiology of chronic arterial hypertension by modifying cardiac output and peripheral vascular resistance [1,2]. It is known that sympathetic nerve activity (SNA) can cause changes in blood pressure (BP) through the activation of baroreceptors [3,4]. Although introduced into scientific practice, methods of SNA evaluation are not commonly used in a clinical setting. Analysis of baroreflex sensitivity (BRS) and heart rate variability (HRV) have been recommended as the diagnostic tools for evaluating SNA and can be found in clinical guidelines as basic assessment methods [5-7]. Data suggest that low BRS and/or HRV are risk factors for cardiovascular morbidity and mortality [8-10].

Increasing clinical evidence suggests that central aortic pressure (CAP), but not brachial BP, predicts cardiovascular events, because the left ventricle (LV) pumps directly against the afterload in the central arteries. Moreover, aortic systolic BP, pulse pressure (PP), and augmentation index (AIx) have been shown to be strong independent cardiovascular risk predictors in hypertensive populations [11-15].

$\beta$ -blockers (BBs) are believed to improve SNS function; however, clinical studies on the effects of BBs on HRV and/or BRS in hypertensive patients have shown mixed results [16,17]. Moreover, it is noteworthy that in a series of studies [14,18-22], atenolol-based therapy was significantly less effective in lowering aortic systolic and pulse pressure than other hypertensive classes, which may be attributed to a different mechanism of atenolol, thus explaining the different clinical outcomes. Since  $\beta$ -blocking drugs might have heterogeneous effects on the arterial system and BRS depending on their pharmacologic properties, further comparisons of the effects of BBs on the arterial system and BRS may be helpful [23]. Bisoprolol with its high  $\beta_1$ -selectivity, long duration of action, and favorable

pharmacokinetic properties was shown to be an effective and safe antihypertensive agent [24,25]. Supposedly, these properties of bisoprolol should be an advantage in clinical practice.

Therefore, the present study was designed to compare the effects of a highly selective  $\beta_1$ -blocker (bisoprolol) and a classical  $\beta$ -blocker (atenolol) on SNA and CAP in hypertensive patients with controlled heart rate.

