#### **7.2.6 Special Tests**

11. Central blood pressure

Central blood pressure was performed by pressure tonometry using the integral software (SphygmoCor; AtCor Medical, Sydney, Australia) at the radial pulse, considering that this system has shown good repeatability of measurements. AIx, a measure of systemic arterial stiffness, was calculated as the difference between the second and first systolic peaks, expressed as a percentage of the pulse pressure. Because AIx depends on heart rate (HR), it was corrected for a HR of 75 bpm (AIxatHR75)

12. BRS, BPV and HRV

Measurements of SNA were performed after a 30-min rest in the sitting position. Patients were monitored noninvasively with a Finometer (Finapres Medical Systems, Amsterdam, The Netherlands; factory number: FMI. MU 00694, 00637; operation parameters: input: 220–240 V, 50–60 Hz, 100 VA) in both the supine (henceforth referred to as ‘lying’) and the standing positions. BRS was defined by the slope of the linear regression curve obtained by plotting the changes of SBP against the pulse interval. The mean value of the various slopes was calculated and used as the definitive BRS value for each subject [5,30-33]. HRV was calculated from the time-sequential analysis and was expressed as 3 components: low frequency (LF), high frequency (HF), and LF/HF ratio.

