#### **8.3.2 Secondary Endpoint(s)**

The secondary endpoints in this study include

- ①. Effective endpoints:
  - i. RHR
  - ii. BPV
  - iii. Blood pressure: peripheral and central blood pressure
- ②. Safety endpoints: AEs recorded in this study
- ③. Compliance Analysis

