### **8.5 Description of Statistical Analyses**

#### **8.5.1 General Considerations**

All statistical tests will be performed at the 0.05 significance level. 95% confidence intervals will be calculated whenever appropriate.

Only available data will be considered for analysis. Subjects who discontinue the study prematurely will be considered as missing data and will be dropped from the statistical analysis.

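### Two primary endpoints are each tested at 0.05 with no rule on whether one or both must be met, and one of them is listed again as secondary

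*Protocol*

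**What the plan says.** Protocol section 8.3.1 defines the primary endpoint in one sentence: "The primary endpoint is BRS and central blood pressure at Last visit". BRS is baroreflex sensitivity. Section 8.5.1 sets the level: "All statistical tests will be performed at the 0.05 significance level". The protocol contains no split of alpha, no order of testing and no statement that one or both endpoints must succeed.

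Section 8.3.2 includes among the secondary endpoints "Blood pressure: peripheral and central blood pressure". The secondary objective on blood pressure (synopsis, section 4 and section 4.2) names peripheral pressure only.

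The variable within each domain is also left open:
- **Central pressure.** The background says that "aortic systolic BP, pulse pressure (PP), and augmentation index (AIx) have been shown to be strong independent cardiovascular risk predictors". Section 7.2.6, under the central blood pressure test, describes AIx and its correction to a heart rate of 75 bpm. Section 8.3.1 picks none of these.
- **BRS.** Section 7.2.6 has patients monitored "in both the supine (henceforth referred to as ‘lying’) and the standing positions". It then says: "The mean value of the various slopes was calculated and used as the definitive BRS value for each subject". It does not say whether the two postures are pooled or which one supplies that value.

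Section 8.1 gives 110 patients, with no effect size, standard deviation or power.

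**The concern.** With two primary tests, the error rate of the trial's main conclusion depends on the success rule, and no rule is given. It could therefore be settled after the results are known. One significant endpoint out of two could be reported as a positive trial, and section 10.6.2 makes the primary endpoint analysis the subject of the first publication.

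This is more than detail left to a statistical analysis plan. Section 8.5.1 is not silent on the level. It fixes 0.05 for all tests, so a later plan that adjusted for two primaries would have to depart from the protocol.

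The second listing of central blood pressure is an inconsistency of its own. The same domain is both primary and secondary, no named variable separates the two roles, and the secondary objectives do not call for it.

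**Working it through.** The protocol states no family-wise error rate and no power calculation, so there is no figure of its own to reproduce.

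**Inputs.** Two primary domains (8.3.1). A level of 0.05 per test (8.5.1). Sidedness is not stated; two-sided is assumed, and the independent-test figures do not depend on it. The correlations are assumptions, shown as a range.

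**Rule A: either endpoint suffices.** If neither drug is better on either endpoint and the tests are independent, the chance of at least one significant result among k tests is 1 − 0.95^k.

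- k = 2: 1 − 0.95² = 1 − 0.9025 = 9.75%.

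For k two-sided tests with common correlation ρ and c = 1.96, the chance is 1 − E{[Φ((c − √ρ·U)/√(1−ρ)) − Φ((−c − √ρ·U)/√(1−ρ))]^k}, with U standard normal. Numerical integration gives:

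| Tests counted as primary | ρ = 0 | ρ = 0.5 | ρ = 0.8 |
|---|---|---|---|
| 2 (one per domain) | 9.75% | 9.1% | 7.8% |
| 4 (one BRS, three central) | 18.6% | 15.6% | 11.4% |
| 6 (two BRS postures, four central) | 26.5% | 20.7% | 13.9% |

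Only the first row follows from 8.3.1 with one variable per domain. The other rows show how the figure grows if further measures are each tested as primary.

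**Rule B: both endpoints are required.** A false joint claim needs a significant result on at least one endpoint with no true difference, so its probability is at most 0.05. The cost is in power. If each test has an assumed 80% power, joint power is 0.80 × 0.80 = 64% under independence. It cannot exceed 80% under positive correlation.

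**Cost of Holm under Rule A.** The first step is at 0.05/2 = 0.025. Assume an effect of 0.54 SD and 55 per arm (110 split 1:1, no losses). Neither the effect nor the resulting power is a protocol figure.
- Noncentrality: 0.54 × √(55/2) = 2.83.
- At 0.05, t critical is about 1.98, so power ≈ Φ(2.83 − 1.98) ≈ 80%.
- At 0.025, t critical is about 2.27, so power ≈ Φ(2.83 − 2.27) ≈ 71%.

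**Listings side by side.** Section 8.3.1 has central blood pressure as primary. Section 8.3.2 has peripheral and central as secondary. The secondary objective has peripheral only. These do not agree, whichever success rule applies.

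**The case against.** The strongest reply is that 8.3.1 is singular and joins its two parts with a conjunction, as does the primary objective. Read that way, both must be met, and with one measure each the error never exceeds 5%. This reading is open, and it rules out calling the inflation a fact. A reader might infer that, as the protocol stands, any one significant result supports a primary claim. The document does not say so: it states neither an either rule nor a both rule, and its objective is to compare. The gap still remains, because a success rule should not rest on how a conjunction is read, and the both-required reading brings a loss of power that section 8.1 does not address.

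Second, 8.5.1 sets the level of each test and promises no family-wise rate. That is correct, so no stated figure is contradicted. The point is that a blanket per-test rule leaves the primary claim uncontrolled under one of the two readings.

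Third, the exact variable, the posture and the multiplicity method are often placed in the analysis plan, which is not at hand. That is fair for the detail. It does not cover the missing success rule set beside a fixed 0.05 for everything.

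Fourth, listing central pressure twice adds no error, since the same test listed twice is one test. This also stands. The double listing is a contradiction to repair and does not inflate the error.

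**Conclusion.** The point holds in conditional form. The protocol names two primary endpoints, gives each test the full 0.05 and states no success rule. If either endpoint suffices, the chance of a false primary claim is about 8% to 10% over correlations from 0.8 down to 0. If both are required, it is at most 5%, with joint power of 64% under independence and an assumed 80% for each. The two listings of central blood pressure conflict under either rule.

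A reader might go further and infer an error of about 26%. The documents do not support that as the trial's error rate. It needs six independent tests, a count the protocol never states. Section 7.2.6 refers to a single BRS value per subject and describes AIx as a measure of arterial stiffness. The corrected AIx may simply replace the raw one. Aortic systolic and pulse pressure as candidates come from the background, not from an endpoint definition. Measures taken from one pulse recording are also likely to be correlated. The 26% is an upper bound for that scenario only.

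This should be fixed. The defensible inflation is moderate and arises under one of two readings.

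**What to change.** All changes are to wording; no visit or measurement is added.

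1. In 8.3.1, name one BRS value, with its posture, and one central pressure variable, both at the Last visit.
2. In the same place, state the success rule. Holm or a fixed sequence at a family-wise 0.05 would serve, as would requiring both endpoints at 0.05 each. Any of these holds the error at 5% or below.
3. Make the remaining central measures and the other BRS posture secondary. In 8.3.2, remove the variable that is already primary and name the central measures that stay. If any stay, widen the secondary objective on blood pressure (synopsis and section 4) to match.
4. Qualify the 0.05 sentence in 8.5.1 so that it agrees with the chosen rule.

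The cost depends on the rule. With Holm, first-step power falls from about 80% to 71% under the assumed 0.54 SD effect and 55 per arm. With a fixed sequence, the first endpoint keeps 0.05, but the second can be claimed only if the first succeeds. With both required, the cost is the joint power shown under Rule B.
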